## Abstract

**Introduction:**

Some clinicians have observed that low-carbohydrate, low-energy diets can improve blood glucose control, with reports of remission from type 2 diabetes in some patients. In clinical trials, support for low-carbohydrate, low-energy diets has been provided by specialist staff and these programmes are unsuitable for widespread deployment in routine primary care. The aim of this trial is to test whether a newly developed behavioural support programme can effectively deliver a low-energy, low-carbohydrate diet in a primary care setting.

**Methods and analysis:**

This is a feasibility randomised controlled trial (RCT) with embedded qualitative study. Thirty adult patients with type 2 diabetes and body mass index ≥30 kg/m^2^ in 2–4 general practices will be randomised 2:1 intervention or control and followed up over 12 weeks. The intervention diet comprises 8 weeks of a low-carbohydrate food-based diet providing around 800 kcal/day, followed by 4 weeks of weight maintenance. This programme will be delivered by practice nurses, who will also support patients through goal-setting, motivation and self-monitoring across four appointments, and provide a self-help booklet with recipes, shopping lists and other behavioural support. Primary outcome measures of feasibility will be met if CIs do not cross the following proportions: that 60% of intervention group participants attempt the dietary intervention, healthcare professionals conduct the intervention delivery session with at least 60% of essential elements present and 60% of participants attend the final follow-up session. Secondary outcome measures will assess process and qualitative measures, as well as exploratory outcomes including change in haemoglobin A1c and change in weight.

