### Sample size

The total number of participants recruited for this study will be 30. As this is a feasibility study, it has not been powered to detect a statistically significant difference in efficacy between the arms. In determining thresholds for progression criteria, based on previous trials of a similar nature, we expect at least 75% achievement.^27 28^ If so, the 95% CI will exclude 60%, and therefore we have set this as the progression criteria for each criterion, requiring a sample size of 30 participants allocated in a 2:1 ratio, intervention:control.

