### Outcomes

#### Primary

The primary objective of this study is to test the feasibility of a low-carbohydrate, low-energy, behavioural intervention, comprising targeted advice from a health professional combined with written dietary information, to promote weight loss and improved glycaemic control in patients with type 2 diabetes. This feasibility study will then determine whether to progress to a full randomised control trial.

The following progression criteria will determine whether to progress to a full trial:That 60% of allocated ‘intervention’ group participants attempt the dietary intervention after randomisation.(Evaluated by documentation after intervention visit; assessed as the proportion of patients who agree to start the dietary intervention, as recorded by the nurse delivering the intervention session.)Fidelity of intervention delivery: That healthcare professionals conduct the intervention delivery session with at least 60% of essential elements present.(Evaluated by assessment of audio recorded consultations against a checklist of pre-specified essential elements.)That 60% of participants attend the final follow-up session.(Documentation of final study visit.)

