### Statistical analysis

Primary outcome measures for this study are progression criteria, to inform any future RCT powered to detect an intervention effect. Analysis for progression criteria will use data from all participants recruited to the trial. Descriptive statistical methods along with inferential statistics presenting CIs will be used to analyse and report progression criteria.

Secondary outcome measures for this study include process measures and exploratory effectiveness measures. Both measures will use all collected data, including that from participants who have not completed the trial, and from participating practices (where pertaining to proportions of patients identified as eligible, and responding to invitations to participate). Descriptive comparative summary statics (eg, difference in means or proportions, together with 95% CIs, comparison with baseline and overall change compared with control group) will be used.

Acceptability and experience of the intervention by participants and healthcare professionals will be collected as qualitative data from interviews and focus groups conducted after intervention completion. These data will be qualitatively analysed using thematic analysis, and reported descriptively.

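### The 60% progression rule is stated inconsistently: with a confidence interval condition in the Abstract, without one in Outcomes, and results near the expected 75% can get opposite decisions

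*Protocol article*

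**What the plan says.** Four sections of the protocol article bear on the rule.

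- **Abstract, Methods and analysis:** "Primary outcome measures of feasibility will be met if CIs do not cross the following proportions". Three 60% criteria follow, joined by a final conjunction. No confidence level and no direction are given.
- **Outcomes, Primary:** "The following progression criteria will determine whether to progress to a full trial". The list is: "That 60% of allocated ‘intervention’ group participants attempt the dietary intervention after randomisation"; "That healthcare professionals conduct the intervention delivery session with at least 60% of essential elements present"; and "That 60% of participants attend the final follow-up session". None carries an interval condition.
- **Sample size:** the investigators write that "we expect at least 75% achievement", and that in that case "the 95% CI will exclude 60" per cent. The sentence goes on to say that this has therefore been set as the progression criterion for each item, with 30 participants allocated 2:1.
- **Statistical analysis:** "Descriptive statistical methods along with inferential statistics presenting CIs will be used to analyse and report progression criteria". It does not say how the interval enters the decision.

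**The concern.** An observed proportion of at least 60% and an interval lying above 60% are different standards of evidence. With 20 or 30 participants, the second needs an observed rate of roughly 77% to 85%. The section that defines the decision states the threshold without the interval, the Abstract states it with the interval, and nothing says which governs. A result between the two standards could then be declared a pass or a fail after it is known. Because progression to the full trial is the trial's primary output, this affects what the trial can conclude.

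A smaller wording fault sits in the Abstract: an interval wholly below 60% does not cross 60% either.

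**Working it through.** **Inputs.** Threshold 60%, expected rate at least 75%, 95% level, and 30 participants at 2:1 (so 20 intervention and 10 control), all from Sample size. Denominators follow the Outcomes wording: 20 for attempting the diet (intervention group only) and 30 for final attendance (all participants). Assumptions: full recruitment, a two-sided interval, and a binomial count. The document names no interval method, so Wald, Wilson and exact (Clopper-Pearson) limits are shown.

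**Step 1. The plan's own statement: at 75%, the 95% interval excludes 60%.** The Wald lower limit is p − 1.96 × √(p(1 − p)/n).

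- n = 20: 0.75 − 1.96 × √(0.75 × 0.25/20) = 0.75 − 0.190 = 0.560.
- n = 30: 0.75 − 1.96 × √(0.75 × 0.25/30) = 0.75 − 0.155 = 0.595.

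Neither excludes 60%. At exactly 75%, Wald needs n = 33. For the whole count 15/20, the intervals are 56.0-94.0% (Wald), 53.1-88.8% (Wilson) and 50.9-91.3% (exact). One-sided 95% lower limits for 15/20 (59.1%, 56.8% and 54.4%) also fall short. The statement is recovered only for n = 30, and only at 23/30 (76.7%), the first whole count above 75%, with Wald limits (61.5-91.8%) or a one-sided limit. It is not recovered for the 20-person criterion, although the section applies it to each criterion.

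**Step 2. Smallest passing count under each reading.** Plain rule: x/n ≥ 0.60. Interval rule: lower two-sided 95% limit above 0.60.

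| Criterion | Plain | Interval, Wald | Interval, Wilson or exact | Opposite decisions |
|---|---|---|---|---|
| Attempt diet, n = 20 | 12 | 16 | 17 | 12-15 (Wald) or 12-16 |
| Final attendance, n = 30 | 18 | 23 | 24 | 18-22 (Wald) or 18-23 |

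**Step 3. Chance of landing in the disagreement range.** This is P(X ≥ plain minimum) − P(X ≥ interval minimum), with X binomial(n, p).

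| True rate | n = 20, Wald | n = 20, Wilson or exact | n = 30, Wald | n = 30, Wilson or exact |
|---|---|---|---|---|
| 75% | 0.959 − 0.415 = 0.544 | 0.959 − 0.225 = 0.734 | 0.978 − 0.514 = 0.464 | 0.978 − 0.348 = 0.630 |
| 80% | 0.360 | 0.579 | 0.236 | 0.390 |
| 85% | 0.169 | 0.351 | 0.070 | 0.152 |
| 90% | 0.04 | 0.13 | 0.01 | 0.03 |

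**Step 4. Leniency of the plain rule.** At a true rate of 50%, P(X ≥ 12 of 20) = 0.252 and P(X ≥ 18 of 30) = 0.181.

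**Step 5. Direction.** The upper limit is below 60% for 7/20 or fewer and for 12/30 or fewer, under all three methods. For example, 5/20 has an exact interval of 8.7-49.1%. Such intervals do not cross 60%.

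**Not computed.** Fidelity is defined as a share of checklist elements present. Neither the number of elements nor the number of sessions is given, so no count threshold or probability can be attached to it.

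**The case against.** The best defence is that the sections complement each other: Outcomes names the criteria and the threshold, and the Abstract and Statistical analysis sections show that the threshold is judged by an interval. Outcomes never says that an observed 60% is enough. The interval method can reasonably be left to an analysis plan that is not shown. Both counts and intervals will be reported, so a reader could apply either rule. This is also a 30-person feasibility study with no efficacy claim at stake.

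Part of this stands. The Outcomes text omits the interval condition rather than denying it, and a charitable reader can carry the condition across. The omission is still in the section that says what decides progression, and no sentence resolves it. Leaving a method to the analysis plan is normal; stating the decision rule differently in two places is not the same thing.

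Several stronger readings are tempting and should not be drawn:

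- A reader might infer that Sample size firmly requires the interval rule. It does not: the thing that was set as the criterion may be the 60% threshold or the exclusion of 60% by the interval.
- A reader might infer that the rules disagree over most plausible results. That depends on the interval method and the true rate. The plan expects at least 75%, so 75% is the floor, and disagreement becomes uncommon by 90%.
- A reader might want a joint probability of meeting all three criteria under each rule. That needs a model for fidelity, such as 20 independent yes/no sessions, which the document does not support.
- A reader might take the missing direction to mean that 5/20 would be declared a success. The expectation of at least 75% in Sample size shows the intended direction; this is loose wording only.

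**Conclusion.** The point holds as an inconsistency in the stated decision rule. It does not show that the plan adopts two deliberate and opposed rules. Its force comes from the planning case itself: 15/20, exactly the expected 75%, gets opposite decisions under the two readings with all three interval methods. At a true 75%, disagreement has probability 54% (Wald) to 73% (Wilson or exact) for attempting the diet, and 46% to 63% for final attendance. At a true 90% the ranges are 4% to 13% and 1% to 3%. These figures rest on full recruitment, denominators of 20 and 30, binomial counts and a two-sided 95% interval. They apply to each criterion separately, and fidelity is outside them. The sample size justification also fails for the 20-person criterion, so adopting the interval rule without correcting it would leave an incorrect statement in place.

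**What to change.** Choose one rule before the data are seen and state it identically in the Abstract, Sample size, Outcomes and Statistical analysis sections. Give the direction, the interval method and level if an interval is used, the denominator for each criterion (including what is counted for fidelity), and the resulting minimum counts.

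- **If the interval rule is kept:** require the lower 95% limit to be above 60%. That means at least 16/20 and 23/30 with Wald limits, or at least 17/20 and 24/30 with Wilson or exact limits. Correct the Sample size section, because 75% of 20 does not exclude 60%. State the chance of passing at a true 75%: 41.5% and 51.4% with Wald, or 22.5% and 34.8% with Wilson or exact.
- **If the plain rule is kept:** remove the interval condition from the Abstract, give the minimum counts of 12/20 and 18/30, and state that a true rate of 50% would pass about 25% of the time (n = 20) or 18% (n = 30).

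A graded scheme with a middle category of amend and review is a reasonable option, but it is not needed to remove the inconsistency. The cost is wording in four sections plus, for the interval rule, a revised sample size paragraph. No extra data are needed.

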**Ethics and dissemination:**

This study has been granted ethical approval by the National Research Ethics Service, South Central Oxford B Research Ethics Committee (ref: 18/SC/0071). The study results will inform whether to progress to a full-scale RCT to test the efficacy of offering this programme for patients with type 2 diabetes in primary care.

**Trial registration number:**

ISRCTN62452621; Pre-results.

Strengths and limitations of this studyThis study directly addresses a key question regarding the dietary management of patients with type 2 diabetes in routine practice.The intervention has been developed by a multidisciplinary team of academic and clinical professionals with patient involvement to create a rigorous yet practical approach suitable for delivery in routine care.Quantitative and qualitative analyses will assess the feasibility of the intervention and inform the development of any future full-scale trial.This study will not demonstrate the clinical effectiveness of this approach, and a subsequent definitive trial will be required to consider whether this intervention can lead to weight loss, improved glycaemic control and diabetes remission.

## Introduction

There are an estimated four million people living with diabetes in the UK, with numbers expected to rise to five million by 2025.^1^ Globally, almost 15% of all deaths in the 20–79 years age group, are attributable to diabetes.^1^ Currently, 10% of the National Health Service (NHS) annual budget is spent on diabetes (around £10 billion). When both direct care and indirect costs are considered, this sum rises to £24 billion, and is predicted to rise further to almost £40 billion by 2035.^1^

Obesity is one of the strongest risk factors for type 2 diabetes,^1^ with an estimated 9% increased risk for every 1 kg of weight gained,^2^ while even modest weight loss of 5% can improve glycaemic control.^3^ For people with established type 2 diabetes, dietary management remains a cornerstone of high-quality care,^4^ aiming to lower blood glucose levels and achieve weight loss in those who are overweight.^3^ There is strong evidence for the benefit of behavioural interventions in the management of type 2 diabetes; a large, high-quality randomised controlled trial (RCT) of over 5000 adults with type 2 diabetes showed that a 12-month intensive behavioural intervention (individual and group meetings to support decreased energy intake and increased physical activity) led to a clinically significant weight loss (mean 8.5% of initial weight, compared with 0.6% in the control group), and a significant reduction in mean haemoglobin A1c (HbA1c; −0.6% (0.55mmol/mol), compared with −0.1% (0.1mmol/mol) (control group)) at 1 year.^5^ The benefits of the intervention were still evident at 4-year follow-up (weight loss of 4.7% and HbA1c reduction of 0.2% (0.2mmol/mol)).^6^ Longitudinal data from the UK Prospective Diabetes Study demonstrates that every 1% (11mmol/mol) reduction in HbA1c is associated with a 21% reduction in risk of diabetes-related mortality, and 37% reduction in risk of microvascular complications.^7^

Weight loss is associated with reduction in HbA1c. Observational analysis of data from RCTs shows that the ORs for a 5%–10% and ≥10% weight loss for a clinically significant 0.5% (0.5mmol/mol) reduction in HbA1c were 3.5 (95% CI 2.8 to 4.4) and 5.4 (4.2 to 7.1), respectively.^8^ The recent Diabetes Remission Clinical Trial (DiRECT) trial demonstrated that with a low-energy, total diet replacement programme (850 kcal/day formula diet for 3–5 months), delivered within a primary care setting and designed to achieve 15 kg weight loss, 46% of participants in the intervention group (compared with 4% in the control group, OR 19.7 (7.8 to 49.8)) achieved diabetes remission at 12 months^9^. However, total diet replacement with a formula product is not acceptable to some patients, some of whom may prefer a food-based diet. In addition, food-based dietary strategies may help establish a sustainable diet for the longer term.

There is limited high-quality evidence for the optimal macronutrient intake for patients with diabetes wishing to lose weight, or improve their glycaemic control.^3 10–12^ Reductions in glycaemic load, through restriction of total carbohydrate and/or changes in the type of carbohydrate to lower the glycaemic index, may have a beneficial effect, due to the direct effect of carbohydrate consumption on postprandial blood glucose levels,^13^ leading to a growing interest in carbohydrate-restricted diets for patients with diabetes. This is reflected in the wealth of recent reviews comparing the effects of low-carbohydrate versus high-carbohydrate diets in patients with diabetes.^11 14–21^ Intervention studies have reported that low-carbohydrate diets can reduce HbA1c by mean 0.5% (0.5 mmol/mol), and body weight by mean 4.8 kg, in people with type 2 diabetes.^14 22^ Recent data from systematic reviews demonstrate that these low-carbohydrate diets may be safe and effective in the short term, yielding greater reductions in HbA1c at 3 (−0.5%, 95% CI −0.7% to −0.2%) and 6 months (−0.4%, 95% CI −0.6% to −0.1%) than higher-carbohydrate diets.^14^ There is no evidence of significant benefit of these diets on HbA1c or weight change at 12 or 24 months,^14^ although the evidence is not precise enough to exclude worthwhile effects on these variables. This apparent diminution in the benefits may be due in part to a decline in dietary adherence over time; additionally, heterogeneity in reporting of medication changes and adjustment for reduction of these in meta-analyses has been suggested to contribute to an underestimation of effect on glycaemic control.^17^ The available evidence has key limitations, including in the variation in definition of what constitutes a ‘low-carbohydrate’ diet, and there remains a lack of pragmatic trials to demonstrate the feasibility of supporting such diets in routine practice. In most trials to date, the programme has been delivered by specialist staff, offering in-depth advice and support which is unrealistic if this is to be delivered at scale.

In spite of the uncertainties in the evidence base, there is considerable interest from patients and the media in using low-carbohydrate diets in the management of type 2 diabetes^23 24^ and some practitioners have begun to recommend patients with type 2 diabetes to follow a low-carbohydrate diet, with or without specific energy restriction.^25^ In 2017, the James Lind Alliance identified the role of carbohydrates, dietary change and how best to support people to achieve these changes, as 3 of the top 10 research priorities in type 2 diabetes.^26^

To address this evidence gap, we will conduct an RCT to investigate the feasibility of delivering a low-carbohydrate, low-energy, food-based dietary intervention in primary care, to patients with established type 2 diabetes and body mass index (BMI) ≥30 kg/m^2^.

The hypothesis is that compared with usual care, an intervention involving targeted health professional advice, goal setting and structured materials, will help patients understand and adhere to a low-carbohydrate, low-energy diet that will lead to significant reductions in weight and associated improvements in glycaemic control (or reduction in diabetic medication required to maintain glycaemic control), providing positive reinforcement of the dietary modification. Few people can maintain a low-energy diet indefinitely (the mean duration of low calorie liquid diet product in the DiRECT study was 16 weeks^9^), but a low-carbohydrate component offers the potential for sustained glycaemic control. Together with the possibility of returning to a low-energy regimen in the case of weight regain, this dietary strategy could provide the foundation for a sustainable approach to the management of this chronic condition.

The specific aims of the Dietary Approaches to the Management Of type 2 Diabetes (DIAMOND) study are to investigate the feasibility of delivering this behavioural and dietary intervention to a population of patients with diabetes in primary care, and determine whether progression to a full-scale RCT is indicated; to assess achievements against a number of process measures to inform future trial design; and to investigate the potential physical, biochemical and economic impact of this behavioural and dietary intervention.

## Methods and analysis

### Design and setting

This feasibility study will be an individually randomised controlled trial, performed in adult patients with type 2 diabetes and a BMI ≥30 kg/m^2^, recruited from general practices in England. Each participant will be enrolled for 3 months from randomisation to final follow-up, and will attend up to seven visits. Due to the nature of the intervention, it will not be possible to blind the participants, clinicians delivering the intervention or some of the study team to the treatment allocation.

### Recruitment

Participants will be recruited from between two and four GP practices for this feasibility study, identified through the regional clinical research network and local expressions of interest. The practices will be asked to search their computerised records to identify people who meet the inclusion criteria. Prior to invitation letters being sent, a general practitioner will screen the list of potential participants to ensure that all those identified are medically appropriate to invite to participate in the trial. The practice will then send potential participants an invitation letter asking them to contact the research team if they are interested, and a participant information sheet with further details about the study.

Participants may also be identified opportunistically during routine consultations or resulting from tests performed as part of the NHS Health Checks programme or diabetes annual review appointments. GPs will provide individuals with the invitation letter and information sheet and invite the individual to ring the study team if they are interested in participating.

Interested individuals will respond to the invitation letter and contact the research team by text, email or telephone. During initial telephone contact, a researcher will discuss the study with the individual and assess self-reported eligibility to participate according to the full inclusion and exclusion criteria as detailed below. They will also establish verbal informed consent for the study team to access the patient’s Oxfordshire diabetic eye screening record, to ensure they meet the retinopathy screening inclusion criteria (as this may not always be coded on the GP’s electronic notes). Eligible individuals who wish to participate will be booked in for a face-to-face baseline appointment.

